### Methods in analysis to handle protocol non-adherence and any statistical methods to handle missing data {20c}

Standard operating procedures have been developed for all study activities and a Clinical Monitoring Plan has been established among UND, CRS, and IDRC. Departures from the protocol that are not participant-specific will be documented in a Protocol Deviation report developed by CRS and reported as required, and the site re-educated as necessary. Any participant-specific non-compliances and other protocol deviations will be captured in the protocol deviation Case Report Form developed by CRS and filed as hard copies. Major protocol deviations will be submitted via email to applicable IRBs and the Sponsor within 24 h of PI becoming aware of them, and followed by a detailed report, within 7 working days.

Significant effort will be made to avoid missing values on the outcome (malaria infection status and visit dates, entomological endpoints). When missing values occur for an outcome for reasons not related to the outcome, reasons for missingness and the missing fraction by treatment arm and cluster will be reported. Per protocol, the participants are screened actively on their malaria status (the outcome) every 4 weeks.

If a participant misses one or more scheduled visits due to reasons not related to SRs or the outcome, the participant will have missing values on the outcome that can be regarded as ignorable missingness (missing at random (MAR) or missing completely at random (MCAR)). If a participant drops out study due to reasons unrelated to SRs and/or malaria infection, then the missing observations from the participant can be regarded as ignorable missingness (MAR or MCAR). In both cases, all available data from the participant will be included in the primary and secondary analysis, without employing any specific technique to deal with the data.

Missing baseline covariates (individual-level, HH-level, cluster-level) that are a part of the regression models for the outcome of interest will be imputed using simple hot-deck imputation methods if the missing fraction for the covariate is < 5%. If the missing fraction for a covariable are ≥ 5%, appropriate multiple imputation approaches will be applied. If a non-ignorable portion of the participants will have missing values on a covariate (due to missing at random or missing completely at random), that covariate may be excluded in the model.

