#### Study personnel distribution channel (reference arm)

In the reference arm, the SR products will be delivered and replaced by paid study personnel throughout the intervention period. The study personnel will distribute the SR every month during a data collection home visit. They will also retrieve used SR to ensure proper disposal of SR. Study personnel will track distribution and retrieval and follow-up on any discrepancies as needed to ensure safe product disposal.

CRS study staff will be employed to ensure proper storage of unused products at site and supply management and coordination for the timely replacement of products in the reference arm. The CRS study team will also perform periodic, unannounced spot checks in a random 10% of enrolled HHs during intervention to monitor SR product compliance (installation according to manufacturer specifications) and ITN usage, if available.

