## Statistical methods

### Statistical methods for primary and secondary outcomes {20a}

The intention to treat (ITT) analysis is the primary analysis approach for both the primary objectives. The ITT population includes the first recruited participant from each recruited HH that receives at least one SR product per the cluster randomization schedule and is analyzed according to the randomization schedule.

The primary objective will be examined by comparing the HRs of the first-time malaria infection between each of the two real-life product delivery mechanisms vs. the reference mechanism in the ITT population. The complementary log–log (cloglog) regression model log(-log(1- Θ_kjit_)) = β_0t_ + **x**^t^_kji_**β**_1_ + z_k_ + z_j(k)_ will be applied. Θ_kjit_ is the discrete time HR of participant i from HH j in cluster k at time t, and x_kji_ contains the individual-, HH- and cluster-level factors that include the treatment group (reference, VHT, voucher) and other relevant covariates (e.g., age, gender, HH type, cluster size, etc.). If the data are extremely unbalanced in a categorical covariate (e.g., 99% HHs had the same type of walls) or if a non-ignorable portion of the participants have missing values on a covariate (due to missing at random (MAR) or missing completely at random(MCAR), that covariate may be excluded in the model. z_k_ ~ N(0,σ_1_^2^) and z_j(k)_ ~ N(0,σ_2_^2^) are the random effects at the cluster and HH levels respectively (z_j(k)_ will be only necessary if some HHs contribute more than one individual to the study).

The difference in effectiveness between each of the two real-life delivery mechanisms vs the reference mechanism will be estimated by exp ($$\widehat{\beta }$$), where $$\widehat{\beta }$$ is the estimated regression coefficient associated with the real-life delivery mechanism compared to the reference. The Wald-type 90% confidence interval will be obtained for the HR along with the point estimate exp($$\widehat{\beta }$$). The cloglog model used to analyze the overall infections is similar to the above model with one modification; that is, the cloglog model will include an additional random effect z_i(jk)_ ~ N(0,σ_3_^2^) to capture the correlation among the overall events from the same participant.

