#### Participants who are hospitalized for serious complicated illness (e.g., chronic illness), die, drop out, or miss scheduled visits due to reasons not related to the malaria outcome or intervention during the follow-up period

For participants that fall under this category, the available data from the participants (up to the time point when the participants are hospitalized, die, or drop out; data from the scheduled visits that the participants did not miss) will be included in both the ITT and PP analyses as the missing or absent data can be ignored.

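### The primary cloglog model makes no allowance for a longer interval after a missed test, so the HR is biased if missed-test rates differ by arm

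*Protocol article*

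**What the plan says.** The primary analysis (Statistical methods {20a}) is a complementary log–log regression with a time-specific intercept, covariates and random effects. Its left-hand quantity "is the discrete time HR of participant i from HH j in cluster k at time t". The printed formula has no offset or other term for interval length. The model for overall infections differs only by one further random effect.

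The testing interval is stated in {20c}: "the participants are screened actively on their malaria status (the outcome) every 4 weeks". In the same section, for a visit missed for reasons unrelated to the product or the outcome, "the participant will have missing values on the outcome that can be regarded as ignorable missingness". The rule that follows is to analyse whatever data that child has, "without employing any specific technique to deal with the data". The paragraph under {20b} on participants who are hospitalised, die, drop out or miss visits agrees: what enters ITT and PP is "data from the scheduled visits that the participants did not miss".

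The article does recognise interval censoring. Its mid-point rule, however, stands in the {20b} paragraph on descriptive incidence rates and is not tied to the cloglog models.

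On how visits differ by arm, the reference-arm section says "The study personnel will distribute the SR every month during a data collection home visit". In the other two arms the product comes separately, by voucher redemption or from a VHT.

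**The concern.** Missingness that is ignorable in the MAR or MCAR sense allows the analyst to work from the observed data, provided that the likelihood for those data is right. In a grouped-time hazard model, the likelihood of a test result depends on how long the child was at risk since the previous test. If one 4-weekly test is missed, the next result covers about 8 weeks.

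If only attended visits become rows and each row counts as one interval, an infection acquired in the gap is still counted as an event, while the missed interval leaves the denominator. The arm's hazard is then overstated. This cancels in the HR when both arms miss tests equally often, and does not cancel when they differ.

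The trial is sized for the precision of the HR around 1, and the Introduction gives equivalence of impact across delivery systems as a purpose. A shift of about 10% produced by the analysis alone would matter for that reading.

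**Working it through.** **1. The plan's own precision.** Inputs from Sample size {14}: 16 clusters per arm, 40 households per cluster, CV 0.40, 10% loss, 0.5 to 1 infection per person-year. The 90% level is from {20a}.

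SE(log HR) = √[(2/16) × (CV² + 1/events per cluster)], with events per cluster = 40 × 0.9 × (1 − e^(−rate)).

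- Rate 0.5: 36 × 0.3935 = 14.2 events; SE = √[0.125 × (0.16 + 0.0706)] = 0.170; 90% CI 0.756 to 1.322.
- Rate 1.0: 36 × 0.6321 = 22.8 events; SE = √[0.125 × (0.16 + 0.0439)] = 0.160; 90% CI 0.769 to 1.300.

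The plan states upper bounds of 1.30 to 1.33 and lower bounds of 0.77 to 0.75, so its precision is reproduced. (The recomputation puts the wider interval at the lower rate, while the text lists them in the other order. This does not affect the present point.)

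**2. Approximate bias.** Let p be the share of scheduled tests missed in an arm. If an undetected infection stays RDT-positive until the next attended test, events are nearly all kept and rows fall to a share (1 − p). The apparent hazard is about h/(1 − p), and the apparent HR is about the true HR × (1 − p_ref)/(1 − p_arm).

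The article gives no missed-test rates, so the pairs below are assumptions.

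**3. Simulation.** 400,000 children per arm, 13 four-week intervals, log-normal frailty with CV 0.4, visits missed independently at an arm-specific rate, infections persisting until detected. A cloglog model with period intercepts and no random effects was fitted to attended visits only, then refitted with an offset for the log number of intervals since the last attended visit. True HR is 1. Ranges cover rates 0.5 and 1.0 per person-year and both first and overall infections.

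| Missed, reference vs operational | Formula | Attended rows only | With offset |
|---|---|---|---|
| 10% vs 10% | 1.00 | 0.99–1.01 | 0.99–1.01 |
| 5% vs 10% | 0.95/0.90 = 1.056 | 1.05 | 1.00 |
| 5% vs 15% | 0.95/0.85 = 1.118 | 1.10–1.11 | 1.00 |
| 10% vs 20% | 0.90/0.80 = 1.125 | 1.11–1.12 | 1.00–1.01 |
| 5% vs 20% | 0.95/0.80 = 1.187 | 1.16–1.17 | 1.00 |

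**4. Dependence on persistence** (5% vs 15%, rate 0.75, true HR 1):

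| Undetected infections clearing per 4 weeks | Attended rows only | With offset |
|---|---|---|
| 25% | 1.07–1.08 | 0.97–0.98 |
| 50% | 1.05 | 0.95 |
| 100% | 0.99–1.00 | 0.90 |

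**5. Against the planned precision.** A factor of 1.11 is log(1.11) = 0.104, which is 0.104/0.17 = 0.61 to 0.104/0.16 = 0.65 standard errors. Coverage of the 90% interval falls to about 83% to 84%. At true HR 1, the interval would centre on 1.11 and run from about 0.85 to 1.44 (SE 0.16) or 0.84 to 1.47 (SE 0.17). A factor of 1.17 cuts coverage to about 74% to 76%.

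**The case against.** The article does not describe how person-interval rows are built after a gap, and the SAP is not shown. An offset might be specified there. This limits the point: that a late positive counts as one interval's event is the literal consequence of the stated rule, not something the article says outright. But the article does not simply leave the matter open. It prints a model without an interval term, keeps attended visits only and disclaims any technique.

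A reader might infer that the HR is biased whenever visits are missed, even completely at random. It is not: randomly missed visits raise the hazard level within an arm, but the HR moves materially only if the rates differ between arms.

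A reader might also infer that the voucher and VHT arms will miss more tests because the data visit offers those families nothing. The documents do not support that. Children in all three arms are tested and get free malaria treatment (Follow-up of the cohort). Tracing, reminders and the ±3-day window apply without distinction by arm. The article does not say that the delivery visit in the reference arm is the routine RDT visit. Differential attendance is possible by design, but neither its size nor its direction is established.

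The ignorability rule covers only visits missed for reasons unrelated to the product or outcome. Staying at home for a delivery is arguably product-related and would fall outside it. The rule still covers unrelated absences, and those can also differ in frequency by arm.

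Sick visits and fever-triggered tests may detect infections earlier, so full persistence is the upper case. Reporting of missingness by arm and cluster is already planned. It would show an imbalance but not correct the HR. The trial is exploratory with no formal test, so the harm is to the estimate and its interval.

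**Conclusion.** The concern holds in a conditional form. The stated rule and printed model make no allowance for unequal intervals between tests, and ignorability of the missed visits does not supply one. If missed-test rates differ by arm, the HR is off by a factor of up to about (1 − p_ref)/(1 − p_arm): roughly 1.05 to 1.12 for the first three unequal pairs, and more for wider gaps. This rests on three assumptions: the missed-test rates, rows built literally from attended visits, and undetected infections staying RDT-positive. The factor shrinks as clearance rises and is immaterial when the rates are equal.

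The documents do not show that the HR will be biased, or that the operational channels will look worse than they are. Nor should a plain offset be read as a complete cure. It over-corrects to about 0.90 at 5% vs 15% if all undetected infections clear, and its behaviour with fever-triggered tests at the second monthly visit was not examined. This is a change worth making before analysis, not a flaw that undermines the design.

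**What to change.** In {20a} and {20c}, for both the first-infection and overall-infection models, replace the no-technique rule with one of these:

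- a grouped interval-censored likelihood, in which the probability of a positive test is 1 − exp(−Σ interval hazards), summed over the intervals since the last completed RDT; or
- an offset equal to the log of time at risk since the last completed RDT.

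State how the person-interval rows are built after a missed test. Add a sensitivity analysis for infections cleared or treated between tests, over a range of clearance. Read the planned report of missingness by arm alongside the HR.

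No new data are needed, since {20c} already lists visit dates with the outcome. The cost is slightly more analysis work and an explicit assumption about persistence between tests.

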### Plans to give access to the full protocol, participant level-data and statistical code {31c}

The Statistical Analysis Plan (SAP) and analytic code will be made open access. Data and supporting information will be made available 12 months following the completion of data analysis and will remain open access in the public domain.

## Oversight and monitoring

### Composition of the coordinating center and trial steering committee {5d}

UND will serve as the lead organization for this program and will assume the overall responsibility for management, oversight, and administration of the program. The coordinating personnel at UND will include the Lead PI, Scientific Director, Program Manager, and Finance Manager. UND will communicate on a day-to-day basis with CRS and IDRC. CRS and IDRC will be responsible for running the study on a day-to-day basis which includes, but will not be limited to deploying SRs and participant follow-up. Representatives from CRS, IDRC, and UND will all serve on the data management team to oversee the development and implementation of data collection, recording, and cleaning.

### Composition of the data monitoring committee, its role and reporting structure {21a}

The DSMB reviews safety data about the cRCT on an ongoing basis in order to monitor and rapidly identify any accumulating safety issues from across the program and may provide recommendations about stopping the study for safety reasons. Additionally, the DSMB provides additional credibility to study quality, by reviewing summary reports from PIs during baseline and intervention phases and making recommendations as needed about adjustments for study quality reasons. The DSMB consists of a Chair, Medical Monitor, DSMB statistician, and independent statistician.

Safety data should be reviewed routinely and regularly by the DSMB Medical Monitor. If significant concern would be raised, he/she can engage with the committee. Summary of AEs, SAEs, and death reports observed during the studies should be reviewed by the entire committee at pre-determined checks (quarterly). This should include a comparison of the rate of AE and SAE in the three study arms and at the individual study site. The DSMB will be notified of any SAEs that are “at least possibly related” to the research study as they are reported to PIs. Unblinded efficacy data will be analyzed according to a pre-defined SAP by an Independent Statistician when pre-defined enrolment targets have been achieved. The role of the DSMB statistician will be to agree to what information will be reviewed (see below) and then review and interpret this information with the other DSMB members, perhaps to request further analysis, for example. The DSMB statistician will contribute input to program PIs as to what subset of the SAP is to be presented at different meetings.

Members generally have no ongoing financial relationship with a trial's commercial sponsor and will not be involved in the trial conduct in any role other than that of a DSMB member. Prospective members will be asked to disclose their financial relationships with any of the sponsors and/or their competitors. The DSMB reports to the Sponsor, UND. The DSMB charter can be made available upon request to UND.

### Adverse event reporting and harms {22}

An AE includes any noxious, pathological, or unintended change in anatomical, physiological, or metabolic functions as indicated by physical signs, symptoms, and/or laboratory-detected changes occurring in any phase of the clinical study associated with the study intervention. This definition includes an exacerbation of pre-existing conditions or events, intercurrent illnesses. A SAE is any untoward medical occurrence that results in death, is life-threatening, results in persistent or significant disability/incapacity, requires in-patient hospitalization or prolongation of existing hospitalization, or is a congenital anomaly/birth defect in the offspring of a study participant. In addition, important medical events that may jeopardize the participant or may require intervention to prevent one of the other outcomes listed above will be considered serious.

All SAEs will be recorded on the appropriate SAE case report form, followed through resolution by a study physician, and reviewed by a study physician.

Symptomatic uncomplicated or severe malaria infection will be coded as AEs as will any other acute illness, throughout the 12 months of the study follow-up phase. Clinical malaria will be recorded in the same fashion as other AEs. In general, uncomplicated malaria will constitute an AE and severe malaria will constitute an SAE. Anticipated day-to-day fluctuations of pre-existing conditions that do not represent a clinically significant exacerbation need not be considered AEs. Discrete episodes of chronic conditions occurring during a study period will be reported as AEs to assess changes in frequency or severity. Pre-existing conditions or signs and/or symptoms (including any that are not recognized at study entry but are recognized during the study period) present in a participant prior to the start of the study will be recorded on the participant’s Case Report Form.

AEs will be documented in terms of a medical diagnosis. When it is not possible to make a specific medical diagnosis, the AE will be documented in terms of signs and/or symptoms observed by the investigator or reported by the participant at each study visit. Any hospitalization will be considered a SAE.

AEs to be recorded as endpoints will be pre-defined based on SCJ toxicology reports of “probable,” “possible,” “plausible,” and “unlikely”:Probable: sensory irritation (oral and dermal)Possible: nausea/vomiting (oral), skin irritation/rash (dermal), runny nose (inhalation)Plausible: salivationUnlikely: eye irritation, headache

AEs and SAEs will be recorded throughout the study. SAEs and the study reports will also be provided to the Makerere University School of Public Health Research and Ethics Committee as required by their current Standard Operating Procedures. AEs will be recorded at time of product replacement and/or when a participant reports for malaria testing. In addition, participants will be informed they can contact study staff anytime they experience an AE. SAEs will be recorded at time of death, hospitalization. Assessment of SAE relatedness to intervention will be conducted by the health facility physician and the study coordinator, in coordination with the local PI in-country with confirmation/verification by the DSMB Medical Monitor based on the study clinician SAE report and trends in other SAE datasets.

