#### Voucher distribution channel

Trained study staff will confirm how many SR products are needed per structure. The voucher will be a small plastic card with a QR and/or barcode that is programmed with the total number of SR products that will be provided monthly to each head of the HH. The head of HH will retain the voucher.

For the initial month of the study, CRS staff will distribute the voucher and provide the SR during a HH visit along with training on product placement and handling. HH heads will be instructed where (central distribution location) and when (every month) they can redeem the SR product(s). For the remaining 11 months, HH heads will redeem their SRs. Vouchers will be redeemed at central distribution locations in the cluster, chosen by the voucher clusters’ community, for example, a health clinic, or food distribution point. Reminders to redeem their SR will be put in place for this distribution channel.

At the central distribution location, the distributor (trained as part of this study) will scan the voucher QR and/or barcode with an electronic device (e.g., tablet or smartphone). By scanning the voucher, the distributor will know and provide the exact number of SR product(s) to distribute to the HH head. The trained distributor will also request that heads of HHs return their old SR product to the central distribution location (for safe disposal) in exchange for the new ones. If there is a discrepancy in the number of returned SR products versus new ones to be issued, the distributors will still issue the total assigned number of new SRs. They will record reasons for the discrepancy. The CRS study Program Manager will then follow-up on these discrepancies to ensure safe product disposal according to the manufacturer’s instructions. If a HH size changes, the HH head will inform the central distribution location or CRS study personnel, which will kick-off a process by which CRS staff will check the new HH dimensions and re-issue a new QR code on a new voucher corresponding to the updated number of SRs to receive.

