#### VHT distribution channel

Uganda’s national community health worker program is organized as VHTs who serve as a HH’s first point of contact for various health-related issues. Working primarily as volunteers, VHTs are ordinary community members who receive basic health care training to provide home visits and health management services. CRS will recruit approximately 32 VHTs to distribute SR, collect and dispose of old SR, and provide HH-level education about SRs. VHTs will be recruited from the existing VHT pool, which was identified and trained by the MOH. Lists of active VHTs are available at the health facilities and with the health cluster lead agency. All the VHTs in the refugee settlement have experience implementing integrated Community Case Management (iCCM) for childhood illness and the provision of other interventions such as ITN, immunization, and health education. Once recruited, the VHTs will receive additional training with regards to study procedures around the SR product itself, how to hang, remove, and safely dispose of it, as well as documenting and monitoring the process. VHTs recruited for study activities will also receive a remuneration for their activities based on locally approved rates.

Upon enrollment into the study, HH participating in clusters assigned to the VHT distribution channel will be visited monthly by a trained VHT. During the home visit, the VHT will distribute the appropriate number of SRs based on measurements for all structures in the HH. They will also retrieve used SR and dispose appropriately. The VHTs will track distribution and retrieval and follow-up on discrepancies as needed to ensure safe product disposal according to the manufacturer’s instructions. During the home visits, VHTs will share key educational information about malaria prevention, the SR, including appropriate placement on the walls, safety, side effects, etc. The study team will check to see if the SRs are hung appropriately and address any issues with the residents. VHTs will address any questions or concerns the participating HH might have.

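### One of the two named occasions for recording adverse events, product replacement, differs by arm, so the between-arm comparison of non-serious events is open to differential ascertainment of unknown size and direction

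*Protocol article*

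**What the plan says.** Adverse event reporting and harms {22} gives the recording rule for non-serious adverse events: "AEs will be recorded at time of product replacement and/or when a participant reports for malaria testing". The same section says that events are recorded throughout the study and that participants may contact staff at any time. Serious events are recorded at death or hospitalisation. Where no diagnosis can be made, an event is documented from "signs and/or symptoms observed by the investigator or reported by the participant at each study visit".

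The intervention sections describe replacement differently for each arm:

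- Reference: "The study personnel will distribute the SR every month during a data collection home visit".
- VHT: "HH participating in clusters assigned to the VHT distribution channel will be visited monthly by a trained VHT".
- Voucher: the first month is a staff home visit. After that, "For the remaining 11 months, HH heads will redeem their SRs". On place, "Vouchers will be redeemed at central distribution locations in the cluster".

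Follow-up of the cohort (under {18a}) has study data collectors visiting every enrolled household every two weeks in all arms. They ask, among other things, about recent illness, and one of the two monthly visits includes a malaria rapid test for every child.

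Safety is a secondary objective (Objectives {7}). Outcomes {12} and Statistical methods {20a} summarise adverse events by channel. The section on the data monitoring committee {21a} adds, at quarterly checks, "a comparison of the rate of AE and SAE in the three study arms".

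**The concern.** A comparison of event rates between arms can be read at face value only if events had the same chance of being noticed and written down in each arm. Here one of the two named recording occasions is itself what the trial randomises. The person present, the place and the informant all change with the arm. In the voucher arm the child need not be there, and an unredeemed voucher removes the occasion.

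The events at issue are mild. The predefined list in {22} includes sensory irritation, rash, runny nose, nausea, salivation and headache. Whether such events are recorded depends heavily on whether someone asks, and when. Staff are not blinded ({17a}). Every arm receives the repellent and there is no placebo, so the contrast between channels is the only comparative safety information the trial will produce. A difference between channels, or the absence of one, could partly reflect how the question was put.

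**Working it through.** The plan states no adverse event rate or capture rate, so there is no figure to reproduce. The check sets the passages side by side and then illustrates the possible effect with assumed values.

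**Step 1. The replacement contact by arm** (intervention sections)

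| | Reference | VHT | Voucher, months 2 to 12 |
|---|---|---|---|
| Who | Paid study personnel | VHT member | Trained distributor |
| Where | Home | Home | Central location |
| Who is met | Household | Household | Household head |
| Part of a data collection visit? | Yes | Not stated; described as the VHT's own visit | No |

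The voucher section lists the distributor's tasks, beginning with "At the central distribution location, the distributor (trained as part of this study) will scan the voucher", then issuing product, collecting used product and recording discrepancies. The VHT section lists delivery, retrieval, tracking and education, including about side effects. Neither lists the recording of adverse events. The rule in {22} is therefore carried out by different people in different places, or its replacement limb is not carried out in two of the three arms.

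**Step 2. What is common to all arms**

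- the two-weekly data collection visit with a question on recent illness
- the monthly rapid test visit, which the words on malaria testing in {22} can cover
- unscheduled sick visits
- the request at consent ({26a}) to report events to a health facility or call the program manager
- contact with staff at any time
- event-triggered recording of serious events

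**Step 3. Illustration.** Assume equal true rates in all arms. Let c be the probability that the common visit captures an event and a the probability that the replacement contact does, independently. None of these values is in the document.

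Captured share = 1 − (1 − c)(1 − a). The apparent rate ratio is the ratio of captured shares.

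*Scenario A: the voucher contact captures less.* Reference a = 0.7; voucher a = 0.3 to 0.5.

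- No common visit: 0.3/0.7 = 0.43 to 0.5/0.7 = 0.71
- c = 0.5: 0.65/0.85 = 0.76 to 0.75/0.85 = 0.88
- c = 0.7: 0.79/0.91 = 0.87 to 0.85/0.91 = 0.93
- c = 0.9: 0.93/0.97 = 0.96 to 0.95/0.97 = 0.98

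*Scenario B: in the reference arm replacement is the data collection visit and adds nothing, while VHT visits are an extra contact.* VHT a = 0.3 to 0.5; reference captured share = c.

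- c = 0.5: 0.65/0.5 = 1.30 to 0.75/0.5 = 1.50
- c = 0.7: 0.79/0.7 = 1.13 to 0.85/0.7 = 1.21
- c = 0.9: 0.93/0.9 = 1.03 to 0.95/0.9 = 1.06

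Scenario A gives ratios below 1 and scenario B ratios above 1. The distortion shrinks towards 1 as the common visit captures more. The document fixes neither c nor a, nor which scenario applies.

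**The case against.** The strongest reply is that replacement is far from the only route. All the contacts in step 2 are the same in every arm. Section {22} counts any acute illness as an adverse event, so a two-weekly question on recent illness is already adverse event ascertainment for much of what will be counted. The reference in {22} to each study visit fits that reading. The between-arm summary is descriptive, with no formal test. Who fills in which form at which visit may also be settled in the full protocol and the operating procedures, which are not shown.

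Most of this stands. It limits the point to mild, non-serious events and makes a large distortion less likely. It does not remove the point. The phrase about each study visit governs how an undiagnosed event is described, and {22} does not name the two-weekly visit as a recording occasion. The question there is about illness, and a caregiver may not count a runny nose or a skin reaction as illness. Outcomes {12} promises solicited reports, but the article does not say that they are solicited in the same way in each arm. The recording rule is a stated one tied to the arm, so this is more than a detail left out of an article.

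**Conclusion.** The rule in {22} makes an arm-dependent contact an occasion for recording adverse events and does not name the contact that all arms share. The planned between-arm summary and the safety board's comparison of non-serious events are therefore open to differential ascertainment. Size and direction cannot be determined from the document. The ranges above rest wholly on assumed capture probabilities and independence between contacts. Serious events are largely unaffected.

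Three stronger readings are tempting, and the document supports none of them:

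- *The comparison is confounded.* That would need replacement to be the only or main route, and several routes are common to all arms.
- *Opportunity to record differs two-fold.* Counting contacts can suggest this: 12 VHT visits on top of 12 to 13 test visits, against 12 to 13 combined visits in the reference arm. It assumes that reference replacement falls on the test visit, whereas the article says only that it falls on a data collection visit. It also assumes that VHT members record events, which their task list does not say. Nor is a ratio of contacts a ratio of captured events.
- *The voucher arm will under-record.* By the same count that arm has the 12 to 13 test visits plus 12 replacement contacts, so it would not have the fewest opportunities.

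This is a modest weakness in a descriptive secondary outcome, worth correcting because the repair is cheap.

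**What to change.** Reconcile the recording rule in {22} with Follow-up of the cohort and with the words in {22} about each study visit:

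1. Study data collectors ask the same predefined adverse event questions at every two-weekly home visit in all three arms.
2. The between-arm summary and the safety board's comparison of non-serious events are based on events recorded at those visits.
3. Events learned of at VHT visits, at voucher redemption, at health facilities or by call are still recorded, but with their source, and are reported separately.

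Serious event recording stays as it is. The cost is a short addition to the visit form and a few extra minutes at visits that already take place. The change is best made before follow-up starts, because analysis cannot recover events that nobody asked about.
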